##### Secondary endpoints

Measurement of grade 3 or higher treatment-related toxicity during or within 24 months after completion of PULSAR, according to the CTCAE v5.0.Disease progression free survival (PFS), defined as the time from enrollment to the first objectively documented disease progression, either in or out of the treated field per radiographic and/or clinical evaluation, or death due to any cause. Participants who experience death or are lost to follow-up prior to 1 year will be assessed by their last radiographic/clinical evaluation.Overall survival (OS), defined as the time between enrollment and death of any cause. Participants who are lost to follow-up prior to 1 year will be censored at the date of their last documentation in the medical record system.Impact of PULSAR on symptoms/quality of life as measured by the UW-QoL and FACT-H&N validated questionnaires.Measurement of the frequency of re-simulation and/or adaptive planning required with PULSAR.Evaluation of the standard of care tumor and OAR dosimetry with PULSAR.Evaluation of the safety and efficacy of combination PULSAR and cancer-directed systemic therapy in enrolled patients receiving cancer-directed systemic therapy will be descriptive and exploratory.

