#### Secondary aims

##### Secondary Aim 1

To evaluate the safety and toxicity of PULSAR as local treatment for patients with de novo or recurrent, localized or metastatic head and neck cancer who are ineligible for or decline standard of care definitive treatment(s).

##### Secondary aim 2

To evaluate the 1-year disease progression-free (PFS) and overall survival (OS) of patients with de novo or recurrent, localized or metastatic head and neck cancer who are ineligible for or decline standard of care treatment(s) who receive PULSAR.

##### Secondary aim 3

To evaluate the symptomatic impact of PULSAR as local treatment for patients with de novo or recurrent, localized or metastatic head and neck cancer who are ineligible for or decline standard of care definitive treatment(s).

##### Secondary aim 4

To determine the frequency of re-simulation and/or adaptive planning required with PULSAR.

##### Secondary aim 5

To evaluate standard of care tumor and organs-at-risk (OARs) dosimetry with PULSAR.

##### Secondary aim 6

To evaluate the safety and efficacy of combination PULSAR and cancer-directed systemic therapy in enrolled patients receiving cancer-directed systemic therapy.

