##### Efficacy analyses

Primary endpoint: Primary endpoint analyses will be performed on patients included in analysis sets FAS and EAS across the whole cohort, as well as separate analyses stratifying patients by Human Papillomavirus/p16 status and receipt of cancer-directed systemic therapy, both in general and by agent type (chemotherapy, targeted, immunotherapy). For the primary endpoint, we will calculate the percentage and construct 95% exact confidence interval for local control rate. Additionally, Kaplan–Meier method and cumulative incidence functions considering distant progression or death as a competing risk will be used to provide estimates of the local control at 1-year, median local control, and cumulative incidence of local control at 1-year, with corresponding 95% confidence intervals.Secondary Endpoints: Secondary endpoint analyses will be performed on patients included in analysis sets FAS and EAS across the whole cohort, as well as separate analyses stratifying patients by Human Papillomavirus/p16 status. For the secondary endpoints of PFS and OS, Kaplan–Meier method and cumulative incidence curves treating death as a competing risk will be used to provide estimates of the PFS/OS at 1-year, median PFS/OS, and cumulative incidence of PFS/OS at 1-year. Corresponding 95% confidence intervals will also be presented.

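### Death is a PFS event by definition, but the plan also scores patients who die at their last evaluation and names death as a competing risk for PFS and OS; these rules conflict

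*Protocol article*

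**What the plan says.** The protocol article makes 1-year PFS and OS the subject of Secondary aim 2: "To evaluate the 1-year disease progression-free (PFS) and overall survival (OS) of patients".

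The Secondary endpoints section defines PFS as time from enrollment to first documented progression, "either in or out of the treated field per radiographic and/or clinical evaluation, or death due to any cause". The next sentence is: "Participants who experience death or are lost to follow-up prior to 1 year will be assessed by their last radiographic/clinical evaluation". The two rules therefore stand side by side in the text: "or death due to any cause. Participants who experience death or are lost to follow-up prior to 1 year will be assessed". The Primary endpoint section uses the same last-evaluation sentence for local control, where death is not an event.

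OS is "defined as the time between enrollment and death of any cause". Its only censoring rule is: "Participants who are lost to follow-up prior to 1 year will be censored at the date of their last documentation". OS has no last-evaluation rule for patients who die.

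For PFS and OS together, the Efficacy analyses section plans Kaplan-Meier estimates and adds that "cumulative incidence curves treating death as a competing risk will be used to provide estimates of the PFS/OS at 1-year". The outputs listed include a cumulative incidence of PFS/OS at 1 year. Nothing in the article says which rule prevails.

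**The concern.** Two statements conflict with the definitions they are meant to serve.

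First, the last-evaluation sentence handles death before 1 year in the same way as loss to follow-up. That suits an endpoint in which death is not an event. For PFS, where death is an event, it gives a second and different answer for the same patient.

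Second, a competing event has to be different from the event of interest. Death is part of the PFS event and the whole of the OS event, so it cannot compete with either.

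At stake is the 1-year PFS reported for Secondary aim 2. The text permits materially different figures from the same data, and the choice could be made after the data are seen. Deaths without documented progression are plausible here. The trial is palliative and admits metastatic disease and poor performance status, and imaging follows standard of care. Post-treatment visits are at 3, 6 and 12 months after the last fraction. Five fractions at the nominal 14-day interval span 4 × 14 = 56 days, so those visits fall at roughly months 5, 8 and 14 from the first fraction.

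**Working it through.** **Stated figure to reproduce.** There is none. The article gives no assumed or target rate for PFS, OS or death. Its sample size concerns local control only and does not bear on this point.

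**One patient under each rule.** Take a patient who dies at month 5 with no progression at the last visit.
- PFS definition: event at month 5.
- Last-evaluation sentence, read literally: progression-free at 1 year.
- Kaplan-Meier with that patient censored at the last evaluation: no event.
- Cumulative incidence with death as competitor: no progression event, so the patient stays on the progression-free side of one minus the curve.

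Each departure from the definition moves PFS upward. None can lower it.

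**Size for PFS (assumed inputs).** Assume constant hazards over 1 year and no loss to follow-up. Let *a* be the hazard of progression and *b* the hazard of death without progression.
- a = −ln(1-year freedom from progression)
- b = −ln(1-year freedom from death without progression)
- PFS by definition = exp(−(a+b))
- Last-evaluation status, or one minus the cumulative incidence of progression = 1 − [a/(a+b)] × [1 − exp(−(a+b))]
- Kaplan-Meier with deaths censored = exp(−a)

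Worked case, 50% and 70%: a = 0.693, b = 0.357, a+b = 1.050. By definition, exp(−1.050) = 0.350. By last evaluation, 1 − (0.693/1.050) × 0.650 = 1 − 0.429 = 0.571. By Kaplan-Meier with deaths censored, exp(−0.693) = 0.500.

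| Free of progression | Free of death without progression | PFS by definition | Last evaluation or competing risk | Kaplan-Meier, deaths censored |
|---|---|---|---|---|
| 50% | 70% | 35.0% | 57.1% | 50% |
| 50% | 90% | 45.0% | 52.3% | 50% |
| 50% | 95% | 47.5% | 51.1% | 50% |

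The overstatement is 22.1, 7.3 and 3.6 points by last evaluation or competing risk, and 15, 5 and 2.5 points by Kaplan-Meier with deaths censored. The first set equals [b/(a+b)] × [1 − exp(−(a+b))], which is exactly the share of patients who die without documented progression.

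**OS.** The cumulative incidence at time t is the integral of (probability of being event-free) × (hazard of the event of interest). If death is the competitor, no OS event remains, that hazard is zero, and the integral is zero at every t. The implied OS is 100% for any mortality. The Kaplan-Meier OS estimate, with death as the event and only loss to follow-up censored, does not have this fault.

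**The case against.** Four points can be made for the plan.

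1. A reader might infer that all the planned PFS and OS figures are wrong. The article does not support that. Kaplan-Meier is named for both endpoints, and for OS the event and censoring rules are sound. Only the added competing-risk output for OS is meaningless. Kaplan-Meier PFS is also right if the definition overrides the last-evaluation sentence. This limit stands in full for OS. For PFS it is conditional on a precedence that the article does not state.

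2. The last-evaluation sentence does not say that patients who die are classed as progression-free. It could mean only that their progression status is taken from the last visit, with the death still counted. That reading is possible, and the matching sentence under local control suggests carried-over wording. It makes the text ambiguous rather than certainly wrong in use, but an ambiguity worth this many points needs resolving.

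3. A reader might take the 22-point gap as the expected error. The documents do not support any single figure. With few deaths before progression the gap is about 4 points, and it depends on which of the planned methods is used.

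4. The endpoints are secondary, and the General section calls all analyses descriptive. No test, sample size or stopping rule depends on PFS or OS. This stands and limits the importance of the point.

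That a separate analysis plan may exist is not an answer. The article states these rules itself, and they conflict as stated.

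**Conclusion.** The point holds in a limited form. The handling of deaths in PFS contradicts the PFS definition. The competing-risk curve is mislabelled for PFS and empty for OS. Kaplan-Meier OS is unaffected, and Kaplan-Meier PFS is correct only if the definition prevails.

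Read literally, the last-evaluation rule can only raise 1-year PFS. The illustration gives about 4 to 22 points by last-evaluation status or competing risk, and 2.5 to 15 points by Kaplan-Meier with deaths censored. This rests on assumed constant hazards, 50% freedom from progression, and 70% to 95% freedom from death without progression. None of these rates comes from the documents.

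The plan should be corrected before analysis, but the matter is not critical: the primary analysis, the sample size and the safety stopping rule are untouched.

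**What to change.** - **Secondary endpoints, PFS:** remove death from the last-evaluation sentence. State that death without prior progression is a PFS event on the date of death, and that patients lost to follow-up alive are censored at their last disease evaluation.
- **Efficacy analyses, secondary endpoints:** estimate PFS and OS by Kaplan-Meier, and drop the competing-risk output for OS. If a competing-risk curve is wanted beside PFS, report it as the cumulative incidence of progression, with death without progression as the competing event.

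The cost is two sentences. The change needs no additional data and no additional patients.

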#### Statistical analysis plan

##### Demographics and baseline characteristics

Demographic data, medical history, other baseline characteristics, and concomitant disease will be summarized. To determine whether the criteria for study conduct are met, corresponding tables and listings will be provided. These will include an assessment of protocol deviations, study treatment accountability, and other data that may impact the general conduct of the study. The analysis sets FAS, EAS, SAS will be used.

##### Efficacy analyses

Primary endpoint: Primary endpoint analyses will be performed on patients included in analysis sets FAS and EAS across the whole cohort, as well as separate analyses stratifying patients by Human Papillomavirus/p16 status and receipt of cancer-directed systemic therapy, both in general and by agent type (chemotherapy, targeted, immunotherapy). For the primary endpoint, we will calculate the percentage and construct 95% exact confidence interval for local control rate. Additionally, Kaplan–Meier method and cumulative incidence functions considering distant progression or death as a competing risk will be used to provide estimates of the local control at 1-year, median local control, and cumulative incidence of local control at 1-year, with corresponding 95% confidence intervals.Secondary Endpoints: Secondary endpoint analyses will be performed on patients included in analysis sets FAS and EAS across the whole cohort, as well as separate analyses stratifying patients by Human Papillomavirus/p16 status. For the secondary endpoints of PFS and OS, Kaplan–Meier method and cumulative incidence curves treating death as a competing risk will be used to provide estimates of the PFS/OS at 1-year, median PFS/OS, and cumulative incidence of PFS/OS at 1-year. Corresponding 95% confidence intervals will also be presented.

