#### PULSAR treatment

Daily cone-beam CT will be obtained prior to radiation delivery to verify anatomic location and stability. Treatment will consist of 6, 10, or 15 MV photons directed at the PTV using HyperArc©’s automated non-coplanar VMAT technique. Patients will receive a total of 55 Gray in 5 fractions (biological effective dose with alpha/beta of 10: 115.5 Gray) to the PTV. Patients will receive each 11 Gray fraction of radiation every 14 +/−10 days. Treatment will be terminated early in cases of intolerable treatment-related toxicity, altered clinical context, or the patient declines further treatment.

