#### Cancer-directed systemic therapy

The following cancer-directed systemic therapy agents alone or in combination are permitted during and after PULSAR in the protocol:Chemotherapy: 5-FU, capecitabine, carboplatin, cisplatin, cyclophosphamide, docetaxel, doxorubicin, etoposide, gemcitabine, hydroxyurea, methotrexate, paclitaxel, vincristine.Targeted agents: Afatinib, cetuximab, dabrafenib erdafitinib, trametinib, vemurafenib.Immunotherapy: Atezolizumab, cemiplimab, durvalumab, ipilimumab, nivolumab, pembrolizumab, tislelizumab, toripalimab.

The specific timing of administration of these cancer-directed agents with respect to delivery of PULSAR fractions, including the decision to hold the agent throughout the entirety of the PULSAR treatment, will be determined at the treating physician(s)’ discretion. Other systemic cancer-directed agents not listed above are permitted at the treating physician(s)’ discretion.

Daily oral systemic cancer-directed agents (e.g. BRAF and MEK inhibitors) may be taken during PULSAR at a frequency determined by the treating physician(s). Example recommendations are provided in the following reference: Guimond et al. [40]*, **Adv Radiation Oncol*. However, coordination of stopping and starting daily oral medications around PULSAR fractions may be challenging, and holding such medications throughout the entirety of the PULSAR treatment is permitted at the treating physician(s)’ discretion.

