#### Patient follow-up

Symptomatic response will be assessed through subjective patient report and completion of the UW-QoL and FACT-H&N questionnaires (Supplemental Material). Treatment-related toxicity during and after completion of PULSAR will be measured according to the CTCAE v5.0. Local tumor response will be assessed clinically and/or radiographically (e.g., by CT, PET, MRI), as applicable. Patient follow-up will be measured starting from the time of trial enrollment. Patient clinical assessments during PULSAR will occur within 7 days of each radiation treatment and consist of brief history, physical exam, and assessment of treatment-related toxicity. After receipt of the last PULSAR fraction, patients will be assessed clinically at 3 months +/- 28 days, 6 months +/- 28 days, 12 months +/- 28 days, 18 months +/- 28 days, and 24 months +/- 28 days post-treatment. These follow-up visits will consist of a history and physical exam, completion of the UW-QoL and FACT-H&N questionnaires, and measurement of toxicity. Surveillance imaging will be obtained per standard of care. Patients who experience disease progression will receive standard of care treatment(s) at the discretion of the treating physician. Patient enrollment, treatment, and follow-up is shown in Fig. 2.

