#### Study endpoints

##### Primary endpoint

The primary endpoint is local control rate of the treated tumor target at 1 year, as measured from the date of enrollment. Local control will be evaluated by radiographic and/or clinical assessment as applicable. Participants who experience death or are lost to follow-up prior to 1 year will be assessed by their last radiographic/clinical evaluation.

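### Strata for the primary endpoint use receipt of systemic therapy at any time, so membership can depend partly on local failure itself

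*Protocol article*

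**What the plan says.** Under Efficacy analyses, the primary endpoint is analysed in the Full Analysis Set (FAS) and the Evaluable Analysis Set for all patients together, "as well as separate analyses stratifying patients by Human Papillomavirus/p16 status and receipt of cancer-directed systemic therapy, both in general and by agent type". The agent types are chemotherapy, targeted agents and immunotherapy. The planned outputs are a percentage with an exact 95% interval, plus Kaplan–Meier and cumulative-incidence estimates. Nothing there says by when therapy must have been given to count as received.

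The section on cancer-directed systemic therapy states: "The following cancer-directed systemic therapy agents alone or in combination are permitted during and after PULSAR in the protocol". Timing is left open, "including the decision to hold the agent throughout the entirety of the PULSAR treatment, will be determined at the treating physician(s)’ discretion". Under Patient follow-up: "Patients who experience disease progression will receive standard of care treatment(s) at the discretion of the treating physician".

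On the endpoint: "The primary endpoint is local control rate of the treated tumor target at 1 year, as measured from the date of enrollment". For early death or loss: "Participants who experience death or are lost to follow-up prior to 1 year will be assessed by their last radiographic/clinical evaluation".

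Two places point to a narrower meaning. The abstract's Methods paragraph speaks of systemic therapy given during PULSAR, and secondary aim 6 concerns the combination of the two treatments. The secondary endpoints and the Descriptive/exploratory analyses section label the combination evaluation descriptive and exploratory.

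**The concern.** HPV/p16 status is a disease characteristic that later events do not change. Receipt of systemic therapy is an event that can occur after enrollment, and the plan treats the two alike. Two mechanisms then link the stratum to the outcome:

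- A patient whose treated tumour fails and who then starts an agent within the year is counted as a failure in the received stratum, although the agent played no part in that failure.
- A patient who starts an agent later without having failed must have stayed failure-free until that start, yet follow-up is counted from enrollment (immortal time).

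The first mechanism makes systemic therapy look harmful and the second makes it look helpful. The net direction cannot be known in advance, so a reader could not correct for it. The Discussion hopes for hypothesis-generating data on PULSAR with immunotherapy as groundwork for later studies, and a gap produced by the classification rule could misdirect that work.

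**Working it through.** **Is there room for the problem?** Fractions are scheduled as follows: "Patients will receive each 11 Gray fraction of radiation every 14 +/−10 days". Five fractions have four intervals, so the nominal course is 4 × 14 = 56 days, or 8 weeks. The endpoint is read at 1 year from enrollment. That leaves at most 365 − 56 = 309 days, about 10 months, less the time from enrollment to the first fraction. An agent started after local failure can easily fall inside that window.

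**The plan's own figures.** The protocol gives no figure for these strata. Its sample size reproduces. With 38 patients, a null rate of 65% and a two-sided exact binomial test, rejection is at 31 or more controlled patients, with actual alpha 0.0398 and power 79.9% at 85%. The strata do not enter that calculation.

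**Size of the artefact when the drugs do nothing.** Let L be the true local control, the same for everyone. Let a be the share on therapy from the start, unrelated to outcome. Of the rest, let b be the share of failures and c the share of controlled patients who start later. As fractions of the cohort:

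- received, controlled: L[a + (1 − a)c]
- received, failed: (1 − L)[a + (1 − a)b]
- not received, controlled: L(1 − a)(1 − c)
- not received, failed: (1 − L)(1 − a)(1 − b)

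The two values of L come from Sample size determination (65% historic control, 85% hypothesised). The values of a, b and c are assumptions; the document gives none. With a = 0.5 and b = 0.5:

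| L | c | Received: controlled / total | Not received: controlled / total | Gap |
|---|---|---|---|---|
| 65% | 0 | 0.3250 / 0.5875 = 55.3% | 0.3250 / 0.4125 = 78.8% | about 23 points |
| 65% | 0.2 | 0.3900 / 0.6525 = 59.8% | 0.2600 / 0.3475 = 74.8% | about 15 points |
| 85% | 0 | 0.4250 / 0.5375 = 79.1% | 0.4250 / 0.4625 = 91.9% | 12.8 points |
| 85% | 0.2 | 0.5100 / 0.6225 = 81.9% | 0.3400 / 0.3775 = 90.1% | 8.1 points |

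**Other start rates.** With a of 30% or 50%, and (b, c) of (30%, 10%), (50%, 10%) or (70%, 20%), the gap runs from 5 to 18 points at L = 85% and from 9 to 32 points at L = 65%.

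**Where it vanishes or reverses.** If b = c the gap is zero. For L = 65% and b = c = 0.5, the received stratum is 0.4875 / 0.7500 = 65% and the other is 0.1625 / 0.2500 = 65%. If c exceeds b, the received stratum looks better.

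**What the illustration leaves out.** It does not model deaths. Under the endpoint rule, a patient who dies early without local failure can count as controlled. If that patient had not started an agent, the death raises the control rate of the not-received stratum.

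**The case against.** The strongest reply is that the article never says ever-receipt. The exposure window of a subgroup variable is the kind of detail a full protocol or analysis plan would fix, and the abstract and secondary aim 6 point to concurrent use. This has some force, but the point is more than a missing detail. The efficacy section states the stratifier without the abstract's limit, and elsewhere the article expressly allows agents after PULSAR. Followed as written, it lets therapy given after failure decide the stratum.

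A second reply is that all analyses are called descriptive, the combination evaluation is exploratory, and no test between strata is planned. With about 43 patients the strata will be imprecise anyway: 17 of 20 controlled would have an exact 95% interval of 62% to 97%. This lowers the severity. It does not remove the bias, which no interval width displays, and strata reported side by side will be compared.

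A third reply is that the follow-up section does not name systemic therapy as the treatment after progression. That is correct. It does not exclude it either, but how many failures would start an agent is an assumption.

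A reader might go further and infer that the strata are simply defined by the outcome, or that any difference between them must be artefact. The documents do not support that. Patients already on an agent before or during PULSAR, ahead of any failure, are classified without reference to later failure, so membership depends only partly on outcome.

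**Conclusion.** The point holds in this limited form. As written, the rule lets stratum membership depend partly on local failure or on time spent free of it. Under the stated assumptions (no drug effect, half treated from the start, half of the remaining failures and 0–20% of the remaining controlled patients starting later), the spurious gap is about 15–23 points at 65% control and 8–13 points at 85%. For scale, the trial's target difference is 20 points. The 23-point figure is the top of that set. It uses the historic-control rate and assumes that no controlled patient starts later, so it should not be quoted alone.

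A reader might also infer that the primary result is compromised. It is not: the whole-cohort analysis, sample size and alpha do not use these strata, and the HPV/p16 strata are not affected by this problem. The change should be made, but for an exploratory analysis it is not critical.

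**What to change.** In Efficacy analyses, define the systemic-therapy strata, in general and by agent type, by therapy status at enrollment. Enrollment is time zero for the endpoint and exists for every FAS patient, including those never treated, who have no first fraction.

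To include agents started during PULSAR, in line with the abstract and secondary aim 6, add a landmark analysis at the last fraction. Restrict it to patients still free of local failure then, and classify them by agents actually given by that date, so that an agent held throughout the course does not count. Do not count therapy first given after local failure or after the landmark as received.

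The change needs a few sentences and agent start dates, and alters no clinical care. The price is smaller received strata and the loss from the landmark analysis of patients who do not reach it. Confounding by indication remains, because physicians choose who gets an agent, so results should still be described as hypothesis-generating.
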